## 3.2. Sample size assumptions and estimates

A systematic review of psychological treatments, mostly CBT, for subthreshold depression yielded a Cohen’s d of 0.42 (95%CI: 0.23 to 0.60) at post-test ([Cuijpers, Smit, & van Straten, 2007](#_ENREF_8)). (a Cohen's d of .42 indicates a treatment effect (difference between control mean and intervention mean on the outcome measure) equal to 0.42 standard deviations (where standard deviation(SD) of interest if the SD of the outcome measure)

| Alpha | power | Effect size | N in each cell  (The allocation ratio = 1:1) | Total N |
| --- | --- | --- | --- | --- |
| 0.05 | 0.90 | 0.4 | 131 | 262 |
| 0.05 | 0.80 | 0.4 | 98 | 196 |

Thus, if we randomize 131 in the intervention group and control group for a total of 262 randomized, we will have 90% power to detect a treatment effect assuming that this difference is equal to .40 standard deviations. However, these calculations ignore dropout. We expect that 75% will complete our six-month follow-up, resulting in 98 respondents in the intervention group and control group at six-month. In this situation, we will have 90% power to detect an effect size equal to .47 SD, which is exactly equal to our best estimate of what effect we expect to see at month 4 in this trial.

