## 3.3. Recruitment of participants

The company representatives and/or the principal investigator will visit study sites and meet with the employees, if possible in small groups, to explain the purpose and rough procedures of the study to increase interest for this program beforehand.

CRC will send out invitation mail to 1700 employees, of whom 680 will give the informed consent, of whom 272 will be candidates (K6>=5), of whom 245 will be eligible. These 245 will be randomized to intervention group (n=122) or to control group (n=123). They will be allowed to complete the six lessons within 10 weeks after the baseline survey. Those on the control group can receive the iCBT only after six-months.

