### 3.3.4. Intervention allocation

We will randomize eligible subjects to intervention and control groups at a ratio of 1:1. Randomization will be stratified on two variables, namely depression severity at baseline (K6=<4 vs. >=5) and center (company A or company B). Assuming that subjects are recruited from 2 sites, there will be a total of 4 strata. The study statistician will prepare 4 lists of random assignments ahead of time, one for each of the 4 strata. Each list will be blocked to ensure that the ratio of intervention to control is exactly 1:1 at set intervals within each stratum. The statistician will send these lists to the research assistant who is not involved in any other aspects of the study and who will build a spreadsheet that enables concealed sequential allocation and will be responsible for keeping these lists in the safe place.

Before randomizing an individual, the CRC will make a final determination of whether or not the person is eligible to be in the randomized trial. For example, prior to randomization, we will exclude those who having major depressive episode in the past a month. Once the CRC determines the eligibility of the participant, she will enter his/her registration number and the stratification variables to the spreadsheet which will automatically generate the allocation according to the pre-determined random sequence. The entered variables cannot be undone in order to guarantee allocation concealment.

Those randomized to control group will be put on a waiting list and after six-month can receive the iCBT if they wish to do so.

One stratification factor is K6>=5 and K6<=4. The cutoff score for K6 selected based on a previous report, which suggested that 4/5 is the optimal cutoff point for K6 in terms of discriminating community residents and patients with mood and anxiety disorders ([Sakurai, Nishi, Kondo, Yanagida, & Kawakami, 2011](#_ENREF_30)).

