### 6.1.3. Analyses of Baseline Data

For continuous and ordinal variables, such as BD1-II and HPQ, we will compute the means for the control and intervention groups and test whether they are significantly different using a t-test. For all yes/no baseline variables, we will compute the percentage yes in each of the two groups and compare using a 1 degree of freedom chi-square test. We may or may not report the p-values from these tests in our "Table 1", which will compare the groups at baseline. Whether or not we report them will depend on the journal that we submit the main outcome paper to since some journals want them reported and some do not.

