### 6.1.4. Analyses of Primary Outcomes

Our two primary outcomes are the BDI-II measure of depression severity and the web-version of the Japanese WHO-CIDI 3.0 measure of the onset of MDE. The BDI-II will be assessed at three- and six-month follow-ups. The Japanese WHO-CIDI 3.0 will be assessed at the six-month follow-up.

The BDI-II is continuous/ordinal variables so will compute the mean score at three- and six-month follow-ups in the two groups, control and intervention. The onset of MDE is discrete variable so will compute the number of incidence at three- and six-month follow-ups in the two groups, control and intervention.

We will first do unadjusted analyses to compare the means using a t-test. We will then do several adjusted analyses. First, ANCOVA or multiple logistic regression analyses will be used to compare the three- and six-month means or the number of incidence on the outcome adjusting for baseline differences on the outcome. We will also do adjusted analyses which control for additional baseline variables, including variables which differ significantly between the control and intervention groups and variables which are strong predictors of the outcome under analysis.

These analyses will be restricted to subjects who complete the three- and six-month follow-ups (all of the statistical methods described above drop from the analysis those with a missing value on the outcome). Since a true intent-to-treat analysis estimates treatment effects based on data from all randomized subjects, not just those who complete a given follow-up, we will also do some mixed-model hierarchical linear models (HLM), using a mixed-model random coefficient model to estimate treatment effects based on all subjects. Subjects are "random effects" with varying intercepts (baseline values) and vary slopes (rates of change from baseline to three- and six-month). The dataset is structured so that each person has up to three records: baseline, three- and six-month follow-ups.

Even subjects who complete only the baseline enter into the analysis and are taken into account when estimating the three- and six-month mean in each group. Such a model can be fit in standard statistical packages such as SPSS, SAS, and STATA.

If conclusions based on the respondent-only and the intent-to-treat analyses are different, we will report intent-to-treat results.

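### Extra covariates are picked by baseline significance or outcome association, no model names the stratification factors, and no single analysis and time point is fixed; the expected cost is small and the fix is wording

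*Protocol*

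**What the plan says.** Protocol section 6.1.4 sets out a sequence for the primary outcomes:

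- an unadjusted comparison (t-test);
- ANCOVA or logistic regression adjusting for the baseline value of the outcome;
- further adjusted models with more baseline variables, "including variables which differ significantly between the control and intervention groups and variables which are strong predictors of the outcome under analysis";
- mixed-model (HLM) analyses on everyone randomised, with up to three records per person.

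The first three use only participants with the follow-up value. BDI-II is compared at three and at six months. The one rule of precedence is that intent-to-treat results are reported if they lead to a different conclusion from the respondent-only results.

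The baseline tests that feed the covariate rule are in section 6.1.3: for continuous and ordinal variables, compute group means and "test whether they are significantly different using a t-test"; yes/no variables get a chi-square test.

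Section 3.3.4 stratifies the 1:1 randomisation by K6 (≤4 or ≥5) and company: "The study statistician will prepare 4 lists of random assignments ahead of time, one for each of the 4 strata". The lists are blocked. Section 6.1.4 names neither factor as a model term. Section 3.1.1 makes K6 ≥ 5 an inclusion criterion, and section 2.3 adds an analysis of the whole sample.

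**The concern.** In a properly randomised trial, any baseline difference between arms arose by chance. A significant one is not evidence that the variable needs adjustment, and a non-significant one is no reason to leave out a prognostic variable. Choosing on observed association with the outcome has a different weakness: unless the variables are named in advance, the outcome data help to shape the model.

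The rule also works against the design. Blocking within strata holds company and K6 level almost exactly balanced between arms, so a test of baseline difference will rarely flag them. They could enter only as strong predictors, or not at all. An analysis that ignores factors used in stratification tends to overstate the standard error.

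Finally, section 2.1 uses the primary outcomes to decide whether the intervention works, while section 6.1.4 offers several models and two time points for BDI-II. If the choice among them stayed open, the chance of a false positive would exceed the nominal 5%.

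**Working it through.** **Inputs from the protocol.** Alpha 0.05, 90% power, effect 0.40 SD, 131 per arm (section 3.2: "0.05 | 0.90 | 0.4 | 131 | 262"). Six-month completion: "We expect that 75% will complete our six-month follow-up, resulting in 98 respondents in the intervention group and control group at six-month". Expected recruitment (section 3.3): "These 245 will be randomized to intervention group (n=122) or to control group (n=123"), so 245 × 0.75 / 2 = 91.9, about 92 completers per arm. Company A has 290 workers and company B about 1,500 invited (section 3.1.2), so company A's share is 290/1,790 = 16%.

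**Assumptions (the protocol gives none).** Two-sided test; baseline–outcome correlation ρ of BDI-II, 0.5 in the main line; share R² of BDI-II variance explained by company, 0.01 to 0.10; similar participation in the two companies.

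**1. The protocol's own figure.** n per arm = 2(1.960 + z)²/0.40². This gives 131.3 for 90% power and 98.1 for 80%, against 131 and 98 stated. The figures reproduce apart from rounding down. They rest on an unadjusted comparison and so do not depend on any covariate.

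**2. Power gained by naming the stratification factors (K6 ≥ 5 population).** The K6 stratum takes one value, so it adds nothing. For company, power = Φ(0.40·√(n/2)/s − 1.960), with s = √(1 − ρ² − R²).

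| Model | 98 per arm | 92 per arm |
|---|---|---|
| Unadjusted | 80.0% | 77.4% |
| Baseline BDI-II (already planned), ρ = 0.5 | 89.9% | 88.0% |
| plus company, R² = 0.01 | 90.2% | 88.4% |
| plus company, R² = 0.02 | 90.6% | 88.8% |
| plus company, R² = 0.05 | 91.7% | 90.0% |
| plus company, R² = 0.10 | 93.5% | 92.0% |

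The gain from company is 0.4 to 2 points for R² of 0.01 to 0.05, and about 4 points at 0.10.

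**3. What those R² values imply.** With shares of 16% and 84%, R² = 0.162 × 0.838 × Δ² = 0.136Δ², where Δ is the difference in mean BDI-II between companies in SD units. R² of 0.01, 0.05 and 0.10 need Δ of 0.27, 0.61 and 0.86.

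**4. Test size when company is left out.** Approximate size of the baseline-adjusted test = 2[1 − Φ(1.96·√((1 − ρ²)/(1 − ρ² − R²)))]. At ρ = 0.5 this is 4.8% for R² = 0.01, 4.2% for 0.05 and 3.5% for 0.10. In simulation at R² = 0.10, ANCOVA on baseline alone rejected in 3.4–3.9% of null trials, against 5.0–5.6% with company included. The error is in the conservative direction.

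**5. Competing analyses.** The simulation used 4,000 null trials per setting, 98 per arm, allocation stratified by company, and eight candidate covariates plus company, selected at p < 0.05 on baseline difference or outcome association. ρ was 0.3 to 0.7, R² was 0.02 or 0.10, and the three- and six-month residuals correlated 0.6. All of these are assumed. Simulation error is about ±0.7 points at 5%.

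| Null rejection | Result |
|---|---|
| Data-selected ANCOVA alone | 4.4–5.5% |
| Fixed ANCOVA (baseline + company) alone | 4.4–5.6% |
| Any of t-test, ANCOVA, selected ANCOVA, one time point | 7.3–9.1% |
| The same, either time point | 12.1–14.7% |

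The last two rows cover completer BDI-II analyses only, without the mixed model or onset of major depressive episode.

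**6. Onset of major depressive episode.** Section 3.1.2 excludes anyone with an episode in the past month. Adjusting the logistic model for that baseline status therefore adds nothing, and the choice of other terms falls back on the selection rule.

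**The case against.** The strongest reply is the precedence rule in section 6.1.4. The t-test and both ANCOVAs are respondent-only; the mixed model is the intent-to-treat analysis. If conclusions agree, they match the mixed model; if not, the mixed model is reported. For BDI-II at a given time point this largely removes the free choice, so a reader who takes 7–9% or 12–15% as the trial's actual false-positive rate goes further than the text allows. This objection stands. What it leaves open is narrower: the protocol speaks of some mixed models without fixing one, gives two time points, and the rule does not clearly reach onset of major depressive episode.

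Four other strong readings are tempting and fail:

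- **A material loss of power.** At 92 per arm, exact-t power is 77.0% for the t-test and 83.8%, 87.6% or 92.1% for ANCOVA at ρ of 0.4, 0.5 or 0.6. Both analyses are already planned, and doing the t-test first sets an order, not a priority.
- **Strata explaining 10–20% of variance.** K6 stratum is constant in the main population, and company alone would need a gap of 0.86 to 1.21 SD between companies. Nothing in the protocol suggests that.
- **Stratification factors excluded from every model.** They are never named, but company could qualify as a strong predictor.
- **The data-selected model inflates error by itself.** In simulation it held about 5%.

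It can also be said that strong predictors may mean variables known beforehand, and that covariate lists usually belong in the statistical analysis plan. Both are fair. But selection by significant baseline difference is a rule the protocol itself adopts, so it is not merely detail left for later.

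**Conclusion.** The point holds in a limited form. Selection of covariates by significant baseline difference is a poor rule that the protocol states outright, and no model names company or K6 stratum although both were used to randomise.

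The expected harm in the K6 ≥ 5 population is small: about 0.4 to 2 power points for an assumed company R² of 0.01 to 0.05 at ρ = 0.5, with a slightly conservative test. K6 stratum matters only in the whole-sample analysis.

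For BDI-II the intent-to-treat rule gives the mixed model precedence. The deciding mixed model, the deciding time point and the analysis of onset of major depressive episode stay unsettled. The rates of roughly 7–9% and 12–15% show what an open choice among completer analyses would cost; they do not estimate the error rate of the plan as written. The correlations, company R² and number of candidate covariates behind all these figures are assumptions.

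The change is worth making because it is free, not because the trial's conclusion is in serious danger.

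**What to change.** In section 6.1.4:

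- Name one deciding BDI-II analysis and one time point. The natural choice is the mixed model on all randomised participants that the protocol already ranks highest, with baseline BDI-II as the first record, arm-by-time terms and company, plus K6 stratum in the whole-sample analysis. Making a completer ANCOVA decisive instead would drop the expected 25% of non-completers and displace the analysis the protocol prefers.
- Include company in the logistic model for onset of major depressive episode, and K6 stratum in the whole-sample version.
- Delete covariate selection by significant baseline difference. List any additional covariates before outcome data are seen.
- Label the t-test, the completer ANCOVA and wider adjustments as sensitivity analyses.

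In section 6.1.3, keep the baseline table descriptive and drop its significance tests.

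The cost is wording only. Baseline BDI-II and K6 are collected in the baseline survey (section 3.3.2), and company is known at randomisation (section 3.3.4).

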### 6.1.5. Analyses of secondary outcomes

Analyses of continuous/ordinal secondary outcomes will be done in the same way as described above: first unadjusted comparison of groups means using t-tests, then ANCOVA comparisons of group means adjusting for baseline values of the outcome, and finally regression analyses which adjust for additional baseline variables. We may also compare group means using mixed-model HLM analyses.

For yes/no outcome variables, we will compare the percentages yes in the control and intervention group first using a chi-square test to do an unadjusted analysis. We will then use logistic regression to do an ANCOVA type analysis which adjusts only the baseline of the outcome. Lastly we will do adjusted logistic analyses which control for other baseline variables.

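### The all-randomised BDI-II model that prevails on disagreement is not tied to a common baseline mean; fitted in the usual way it is less precise than the completer ANCOVA it can overrule

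*Protocol*

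**What the plan says.** Section 6.1.4 of the protocol plans two kinds of analysis for BDI-II.

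- **Completers only.** An unadjusted t-test, then ANCOVA with the baseline score as covariate, then models with further covariates.
- **All randomised subjects.** A mixed random-coefficient model. Baseline is a response here: "The dataset is structured so that each person has up to three records: baseline, three- and six-month follow-ups". The subject-level effects are "varying intercepts (baseline values) and vary slopes (rates of change from baseline to three- and six-month". The section adds that people with a baseline record alone still contribute to the estimated follow-up means in each group.

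A precedence rule links them: "If conclusions based on the respondent-only and the intent-to-treat analyses are different, we will report intent-to-treat results". The reason given is that only the second analysis uses everyone randomised.

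The section does not write out the fixed effects. It does not say whether arm means may differ at baseline, or which quantity (slope difference, change, or follow-up mean) is the treatment effect. For continuous secondary outcomes, section 6.1.5 leaves the model optional: "We may also compare group means using mixed-model HLM analyses".

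**The concern.** The two analyses may use the same baseline score differently. ANCOVA uses it to remove outcome variance. A mixed model with arm, time and arm-by-time terms estimates a separate baseline mean in each arm. Its six-month effect is then either the difference in change from baseline or the difference in estimated six-month means. Neither uses the fact that randomisation makes the expected baseline equal in the two arms.

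The precedence rule makes this matter. It is meant to protect against selective dropout. If the model that prevails is also the less precise one, some disagreements will arise only from its larger standard error. They could be read as a missing-data problem, and an effect that ANCOVA detects could be reported as not shown.

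**Working it through.** **Planned size reproduced first.** Section 3.2 gives the rows "0.05 | 0.90 | 0.4 | 131 | 262" and "0.05 | 0.80 | 0.4 | 98 | 196". With a two-sided 5% test (sidedness is not stated), n per arm = 2(1.960 + 1.282)²/0.4² = 131.3 for 90% power, and 2(1.960 + 0.842)²/0.4² = 98.1 for 80%. Both match. With 98 per arm, the effect detectable at 90% power is 3.242 × √(2/98) = 0.463 SD, against the stated 0.47. These are comparisons of two means without baseline adjustment.

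**Inputs from section 3.2.** 131 randomised per arm, an effect of 0.40 SD, and dropout: "We expect that 75% will complete our six-month follow-up, resulting in 98 respondents in the intervention group and control group at six-month".

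**Assumptions.** SD 1 at each visit; equal correlation r between visits (not given in the protocol, so a range is shown); the 33 dropouts per arm have baseline only; dropout completely at random; large-sample variances.

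**Six-month variance per arm.** With baseline means free, an arm's estimated six-month mean is the completers' mean, shifted by r times the gap between the baseline mean of all randomised and that of completers. This gives:

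- completer ANCOVA: (1 − r²)/98
- mixed model, change contrast: (1 − r²)/98 + (1 − r)²/131
- mixed model, six-month-mean contrast: (1 − r²)/98 + r²/131
- mixed model, common baseline mean: (1 − r²)/98, because the baseline mean cancels between arms

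**At r = 0.5.** ANCOVA: 0.75/98 = 0.007653. Either free-baseline contrast: 0.007653 + 0.25/131 = 0.009561. The ratio is 1.25. For two arms the standard errors are √(2 × 0.007653) = 0.124 and √(2 × 0.009561) = 0.138. Power is Φ(0.4/0.1237 − 1.96) = 89.9% against Φ(0.4/0.1383 − 1.96) = 82.4%.

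**Over the range of r:**

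| r | Variance ratio: change | Variance ratio: six-month mean | Variance ratio: common baseline | Power: ANCOVA | Power: change | Power: six-month mean |
|---|---|---|---|---|---|---|
| 0.3 | 1.40 | 1.07 | 1.00 | 83.5% | 69.8% | 80.8% |
| 0.5 | 1.25 | 1.25 | 1.00 | 89.9% | 82.4% | 82.4% |
| 0.7 | 1.13 | 1.72 | 1.00 | 97.5% | 95.8% | 84.9% |

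The ratios are relative to completer ANCOVA. The common-baseline model has the same power as ANCOVA.

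**Variations.**

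- With time linear and baseline free by arm, six times the slope difference has ratios 1.40, 1.25 and 1.13, the same as the change contrast.
- If 16 of the 33 dropouts have a three-month record, the common-baseline ratio is 0.97 to 0.99 for r from 0.3 to 0.8.
- With complete data, the ratios are 2/(1 + r) for change and 1/(1 − r²) for the six-month mean, both 1.33 at r = 0.5.
- Section 3.3 expects 245 randomised. The ratio at r = 0.5 hardly changes, and power is about 88% against 80%.

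**Disagreement.** Under these assumptions each free-baseline contrast equals the ANCOVA estimate plus independent noise, so the two estimates correlate at √(1/1.25) = 0.89 when r = 0.5. With a true effect of 0.40 SD, the bivariate normal gives ANCOVA significant and the mixed model not in about 9% of trials, and the reverse in 1 to 2%.

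**The case against.** The strongest objection is that the protocol does not specify the imprecise model. A three-record dataset is a layout. The random intercepts and slopes describe subjects, not fixed arm effects. A common-baseline model uses exactly the same records and loses nothing. The fixed effects may properly stand in an SAP that is not shown. All of this is correct. A reader might infer from the three-record sentence that the loss is built in, but the text does not support that. What stands is narrower: the section fixes the model class, the response records and the precedence rule, describes the slopes as change from baseline, and does not carry the ANCOVA's baseline adjustment over. The conventional fit of that description has the loss.

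Four further points limit the concern:

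- **Size depends on r and on the contrast.** The change contrast does worst at low r and the six-month-mean contrast at high r. No single row of the table should be taken as the headline.
- **Planned power is not generally undercut.** The sample size is unadjusted, with 98 per arm for 80% power at 0.40 SD. At r = 0.5 both free-baseline contrasts still have 82%. Only the change contrast at lower r falls short (69.8% at r = 0.3).
- **The precedence rule is not shown to be wrong.** The comparison assumes dropout completely at random, where completer ANCOVA is unbiased. The rule exists for the case where dropout is selective, which the protocol's analysis of non-response takes seriously.
- **Disagreement is not frequent.** A reader might infer that the two analyses will often conflict. About 9% in one direction at r = 0.5 does not support that.

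**Conclusion.** The point holds in conditional form. Section 6.1.4 gives precedence to an all-randomised BDI-II model without stating a common baseline mean or a baseline covariate. If baseline means are left free by arm, the six-month variance exceeds that of completer ANCOVA by 13% to 40% for the change contrast and 7% to 72% for the six-month-mean contrast, over assumed r from 0.3 to 0.7. At r = 0.5 the excess is 25% for both, and power for 0.40 SD is about 82% rather than 90%. These figures rest on 131 randomised and 98 completers per arm, baseline-only dropout completely at random, and equal correlation between visits.

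No bias or type I error problem is claimed, and nothing here says that ANCOVA should prevail. Some disagreements between the analyses would reflect only the difference in precision, not missing data. The point concerns BDI-II, and continuous secondary outcomes if the mixed model is used for them. It does not concern onset of MDE. It is worth acting on because it improves the prevailing analysis with a baseline value already collected.

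**What to change.** In section 6.1.4, state that the all-randomised BDI-II model has one baseline mean common to both arms: visit effects, plus arm effects at months three and six only, with no arm effect at baseline. Report the arm difference with its confidence interval at each of the two visits. Keep the precedence rule as it is. In section 6.1.5, use the same form for continuous secondary outcomes wherever the mixed model is fitted.

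The cost is one or two sentences. No new data are needed, and baseline-only subjects stay in the analysis. Precision equals that of completer ANCOVA, or is slightly better where dropouts have a three-month record.
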